### Study procedures and required materials

#### Enrolment of study participants and sample collection

Individuals seeking for COVID-19 testing at the reference sample collection sites will be provided with an information notice on the present study; detailed explanation on the study with be done to each of the potential participant, and then a written informed consent will be signed prior to enrollment. Eligibility criteria will then be verified as aforementioned for consideration as study participants. Nasopharyngeal/oropharyngeal swabs and blood/serum specimens will be collected for each eligible participant. Swabs will be stored in the viral transport media (for real time PCR) while blood/serum will be stored in test tubes (for serology/rapid testing respectively). Collected samples will be kept on cold chain and transported to the reference laboratory unit by well-trained personnel.

#### Establishment of well-characterised respiratory and sera specimens of COVID-19 positive cases

Training of staffs on sample collection procedure, transportation, storage and monitoring conditions will be done as previously described by Wang et al., 2020 [6]. Specimens of oropharyngeal and nasopharyngeal specimens, whole blood/serum, will be collected by trained staffs of the CIRCB in Cameroon.

#### Serological and antigen testing of COVID-19 suscepted cases: Antibody-based testing

For now, there are about five antigen-detection RDTs and 27 antibody-detection RDTs that have been selected for the first round of evaluation worldwide (and more are in evaluation), following approvals by FDA and EUA, and consideration for assessment by the Foundation for Innovative New Diagnostics (FIND), available at https://www.finddx.org/covid-19/sarscov2-eval-immuno/.

Based on preliminary results on 100 samples, five most efficient commercially available serological tests (Elisa tests: Dia.Pro COVID-19 IgG/M + confirmation and Aliphax WANTAI SARS-CoV-2; CLIA: Diasorin CLIA LIASON SARS-CoV2SI/S2 IgG; Rapid: Aliphax Cellex q Rapid Test; VivaDiag COVID-19 IgM/IgG rapid Test) were selected, with sensitivity and specificity ranging between 75%-98%. Antigen detection tests to be evaluated are LumiraDx Ag, Panbio COVID-19 Abbott Ag Rapid Test and Standard Q COVID-19 Ag Test Biosensor. Based on local neeeds, INDICAID AgRDTs (Phase Scientific), Ninonasal AgRDTs (NG. BIOTECH Laboratories) and NG.TEST/IgG-IgM COVID-19 (NG. BIOTECH Laboratories) could be considered.

#### Molecular testing of COVID-19

Molecular testing entails conventional real-time PCR, point-of-care GeneXpert Express (Cepheid), ddPCR as well as sequencing reactions. For all molecular testing and sequencing, viral RNA was extracted from respiratory samples using the QIAmp viral RNA Mini kit (Qiagen Hilden, Germany) according to the manufacturer’s protocol.

*Real-time qRT-PCR for SARS-CoV2 testing*. This protocol is designed to detect SARS-CoV2 in human clinical specimens. The two monoplex assays are reactive with the 2019 novel coronavirus, considering: (1) the genetic diversity of 2019-nCoV in humans and animals, (2) the use of an internal control, (3) the kit being widely available across SSA. Amplification will be performed on Applied Biosystem/Thermocycler devices (TheromFisher, ViiATM 7 Real-Time PCR), with a positive control, primer sets, primer and probe sequences. The amplicon sizes of Assay 1 and Assay 2 are 132 bp and 110 bp, respectively. Interpretation of positivity of N gene RT-PCR and Orf1ab is done at required cycle thresholds (Sun Yat-sen University protocol). A negative N gene positive/Orf1b refers to the absence of SARS-CoV2. Results will be evaluated with reference to ddPCR.

*GeneXpert for SARS-CoV2 testing*: *Xpert*^*®*^
*Xpress SARS-CoV-2*. Xpert^®^ Xpress SARS-CoV-2 is a test that has the Food and Drug Administration (FDA) emergency use authorization (EUA). Xpert^®^ Xpress SARS-CoV-2 is currently the most prominent test for real-time RT-PCR rapid test for SARS- CoV-2 developped by Cepheid, which provides results in just 45 min using GenXpert benchtop system. It is a rapid and automated point-of-care (POC) molecular test that enables the qualitative detection of SARS-CoV-2 in nasopharyngeal swab, nasal wash, or aspirate specimens from COVID-19 suspects. The test requires only a minute for sample preparation, employs cartridges, and targets multiple regions of the viral genome. Accuracy will be evaluated using ddPCR as gold standard.

*Use of ddPCR SARS-CoV-2*. Droplet digital PCR (ddPCR, Bio-Rad) is an innovative low-cost molecular assay delivering results within 2 hours, for timely clinical decision. ddPCR is based on the principles of limited dilution, end-point PCR, and Poisson statistics, with absolute quantification [32–36]. The single-step ddPCR detects COVID-19 genome at very low copies number, representing a chance to detect infected subjects before symptom onset, including their close contacts. ddPCR system will use a set of primers and probe sets, in order to ensure viral detection at early stages, for timely management. The developed ddPCR will serve for the linear quantification not only of viral genome but also intermediate of viral replication such as subgenomic RNAs. Negativity of these intracellular markers will serve as surrogate of viral clearance, a crucial aspect in breaking the transmission chain. This type of second level diagnosis requires a practical training of staff, with hands-on, in collaboration with expertise in molecular virology within the network in place.

#### Illumina next generation sequencing

Through Next Generation Sequencing (NGS), the entire SARS-CoV-2 genome will be characterized. The use of an NGS Core (equipped with MiSeq, NextSeq500 and NovaSeq 6000 and Bioinformatics Core) will be set up to determine the variability of the entire sequence of SARS-CoV-2 genome in patients’ samples. This approach will ensure a full analysis of all intra-host viral variants (even those with low prevalence), thanks to its high-throughput performance and to define the evolution of SARS-CoV-2 epidemic in SSA.

Sequencing of the entire viral genome will be performed in a subset of 50% (n = 384) selected samples nasopharyngeal swabs with multiplex PCR and sequencing (1,000x coverage). Viral genome sequences will be obtained by NGS and analysed along with sequences collected from GISAID database (https://www.gisaid.org/). Similarly, full-length sequences of other human SARS-related coronaviruses and those isolated from animal species, known as natural reservoirs of coronaviruses, will be retrieved from GenBank (http://www.ncbi.nlm.nih.gov/genbank/).

Multiple phylogenetic trees will be constructed by RaxML and MrBayes programs to estimate the evolutionary rates along the entire SARS-CoV-2 genome and to calculate the divergence between SARS-CoV-2 and other related human and animal coronaviruses, by setting best-fit substitution models (nucleotide and amino acids). The ratio of non-synonymous and synonymous substitutions (dN/dS) will be analysed across the whole sequences of all SARS-CoV-2 coding regions McDonald-Kreitman Test. This analysis will allow to identify viral regions enriched of sites under negative selective pressure, thus less prone to accumulate amino acid mutations. Shannon Entropy (Sn) will be also calculated as additional measure of the extent of amino acid variability at each position of SARS-CoV-2 proteins. Evolutionary divergence of the different genetic viral regions will be also estimated as the extent of nucleotide substitutions per site determined by the Tajima-Nei model [37]. These bioinformatics analyses are also geared toward conserved/negatively selected regions of SARS-CoV-2 shared also by the other coronaviruses, for optimal antiviral drug candidates and vaccine targets for pan-coronaviruses.

This study will also take advantage of a large clinical cohort including patients with a well-characterized clinical and virological history for SARS-CoV-2 related disease and with an available SARS-CoV-2 full-length sequence. These patients will be stratified according to the severity of SARS-CoV-2 clinical manifestations (pneumonia vs mild respiratory symptoms). Each nucleotide and amino acid mutation detected in SARS-CoV-2 genome sequences will be analyzed by using an advanced mathematical model developed in collaboration with Yale University. In particular, we will apply a Bayesian variable partition model, and a recursive model selection procedure (according to Zhang et al., PNAS 2010) in order to define mutations either independently or interactively correlated with the severity of SARS-CoV-2 manifestations. Thus, this mathematical model will allow identifying not only single mutation also clusters of mutations in multiple viral genes correlated with cov-2 related severe pneumonia. A multivariable logistic regression analysis will be also carried out in order to support the correlation of the identified mutations and other clinical and virological parameters with SARS-CoV-2 disease severity. Once more, such second-level diagnosis requires a thorough practical training of staff, in collaboration with experts within the netwrok in place.

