**The specific objective** 1 will provide on the evidence on the performance of conventional real-time qRT-PCR platforms and Xpert Xpress SARS-COV-2 Test (Cepheid), when compared to ddPCR system results, for use as support to the global efforts in controlling COVID-19 pandemic in SSA; evidence on correlations between cycle thresholds obtained by conventional real-time qRT-PCR platforms and Xpert Xpress SARS-COV-2 Test with SARS-CoV-2 load by absolute ddPCR quantification for adapting the interpretation of SARS-CoV-2 results in sub-Saharan African countries; and evidence on available point-of-care molecular assays achieving a desirable performance for the detection of SARS-CoV-2 in resource-limited settings like sub-Saharan Africa.**The specific objective 2** will provide evidence of antigen-based assays (like LumiraDx, Panbio COVID-19 Abbott Ag Rapid Test and Standard Q COVID-19 Ag Test Biosensor) performance to allow for accurate and rapid detection of early/acute COVID- 19 cases; evidence of antibody-based assays for a timeous SARS-CoV-2 sero-surveillance in SSA; and types of antibody-based assays appropriate for assessing exposure and/or immune response following SARS-CoV-2 infections.**The specific objective 3** will generate knowledge on the circulating strains of SARS-CoV-2 in West and Central Africa, and their potential differences with SARS-CoV-2 strains found in other settings; effects of the SARS-CoV-2 genetic diversity on vaccine development at global level, and/or at continental level; phylogeography and phylodynamic of SARS-CoV-2 strains for understanding the migration of the virus toward effective preventive interventions, identification of clusters of transmission and optimal surveillance; and understanding of the clinical significance of SARS-CoV-2 genetic diversity to rate of recovery or risk of severity and mortality among COVID-19 confirmed cases.**The specific objectives 4–6** will provide timely inform policy-makers on SARS-CoV-2 confirmation molecular assays for decision-implementation within the national territory, and possible in other West and Central African countries; proposition of a potential serial or parallel algorithms for SARS-CoV-2 detection using rapid testing approach; definition of the diagnostic strategy with the highest level of accuracy for a molecular and a rapid test for the detection of SARS-CoV-2; notification of immunodiagnostic assays suitable for technical triage/screening of SARS-CoV-2, thus reducing costs and increasing testing capacity for resource-limited settings; as well as informed decision on testing approaches with suitable efficiency and turn-around time.All the study protocols here described, especially for evaluation of assays, will be adapted to future comprehensive WHO guidances once published.

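### The logistic regression meant to support the selected severity mutations apparently reuses the patients and outcome that selected them, so it adds almost no independent evidence

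*Protocol article*

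**What the plan says.** The plan for this analysis is in the protocol article, under Illumina next generation sequencing.

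- **Data.** One source is named: "This study will also take advantage of a large clinical cohort including patients with a well-characterized clinical and virological history". Its size is given only as large. The patients are divided into pneumonia and milder respiratory illness.
- **Search.** "Each nucleotide and amino acid mutation detected in SARS-CoV-2 genome sequences will be analyzed by using an advanced mathematical model". Specifically, "we will apply a Bayesian variable partition model, and a recursive model selection procedure", and the purpose is stated: "in order to define mutations either independently or interactively correlated with the severity of SARS-CoV-2 manifestations".
- **Second step.** "A multivariable logistic regression analysis will be also carried out in order to support the correlation of the identified mutations", together with other clinical and virological parameters, with severity as the outcome.

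No second cohort, split sample or selection-adjusted inference is mentioned. The Statistical analysis section adds confounder adjustment by logistic and linear regression. Expected outcomes then promises an understanding of the clinical significance of SARS-CoV-2 "genetic diversity to rate of recovery or risk of severity and mortality among COVID-19 confirmed cases".

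**The concern.** The protocol gives the regression a specific job: to support what the search found. It can do that only if it brings information that the search has not already used. If the mutations were chosen because they correlate with severity in these patients, regressing severity on them in the same patients largely repeats the selection criterion. The usual p-values and intervals treat the covariates as fixed in advance, so they are too optimistic after selection. Adjusting for age, sex or other clinical variables does not remove this.

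This is a matter of what the stated sequence of steps delivers, not of missing detail. At stake is the credibility of any reported link between particular mutations and severe disease, because a reader would take agreement between the two methods as corroboration.

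**Working it through.** The protocol gives no sample size, error rate or power for this analysis, so there is no figure of its own to reproduce. The check asks: if no mutation is related to severity, how often does the second step support a mutation that the first step picked?

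**Inputs**

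- Patients: 384. This is an assumption, borrowed from the study's own sequencing subset in the same section; the severity cohort's size is not stated.
- Severe share: 20% (also 50% in the second simulation). Assumption.
- Candidate sites M: 30, 100 and 300 (100 and 500 in the second simulation). Assumption.
- Carrier frequency: 5% to 50%, sites independent. Assumption.
- Supporting regression: two-sided 0.05. Assumption, in line with the 95% intervals used elsewhere in the protocol.

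**Step 1. Scale of the search.** With M independent null sites screened at 0.05, the expected number of false hits is 0.05 × M, and the chance of at least one is 1 − 0.95^M.

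- M = 20: 1 expected; 1 − 0.95^20 = 0.64.
- M = 100: 5 expected; 1 − 0.95^100 = 0.994.
- M = 500: 25 expected; about 1.0.

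**Step 2. Five strongest sites carried forward.** The top five sites by marginal association go into one multivariable logistic regression (500 null datasets per row). This is a stand-in for the Bayesian search. The table gives the share of selected sites with p < 0.05.

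| Candidate sites | Same patients | Held-out half |
|---|---|---|
| 30 | 27% | about 4% |
| 100 | about 70% (68% to 71% over repeat runs) | about 4% |
| 300 | 93% | about 4% |

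The held-out figures varied between 4% and 5% over repeat runs, close to the nominal 5%.

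**Step 3. Selection by threshold, so that a dataset may yield nothing.** M = 100 or 500, severe share 20% or 50%, regression adjusted for age and sex.

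| Selection rule | Selected null sites supported, same patients | Null studies with at least one site selected and supported, same patients |
|---|---|---|
| p < 0.05 | 73–77% | 97–100% |
| p < 0.01 | 98–100% | 64–99.5% |
| Bonferroni | 100% | about 5% |
| Approximate posterior > 0.5, prior odds 1/M | 100% | 0.6–1.7% |

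In held-out patients the supported share is about 3–6% after the two looser rules. After the two strict rules it is 0–13%, but that rests on only 10 to 100 selections per scenario.

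**Step 4. Why the last rule passes so little.** With the BIC approximation, a posterior above 0.5 at prior odds 1/M needs a likelihood-ratio chi-square above ln(N) + 2 ln(M).

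- M = 100: 5.95 + 9.21 = 15.16, p = 0.0001; 100 × 0.0001 = 0.01 expected null selections per study.
- M = 500: 5.95 + 12.43 = 18.38, p = 0.000018; 500 × 0.000018 = 0.009.

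Both agree with the simulated 0.6–1.7%. A site that clears such a bar in these patients will nearly always clear 0.05 in the same patients, so the regression adds almost nothing to the search, however strict the search is.

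**The case against.** The strongest reply is that the simulations do not model the planned method. Forcing five selections in every null dataset builds in false hits, whereas a Bayesian partition model may select none; under the posterior-type rule above, only about 1–2% of null studies select anything. This stands. A reader might infer that the analysis would report severity mutations when none exist, or that chance associations are confirmed almost automatically. The documents do not support that unconditionally: it applies to chance hits that pass the search, and the prior and cut-off governing that are not given. With 30 sites even the forced selection gives 27%.

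Other parts of the reply also stand:

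- Use of the same patients is inferred. It is, however, the only reading the section offers, since one cohort is named.
- A reader might conclude that the result feeds drug and vaccine targets. In the sequencing section that aim belongs to the conserved-region analyses, which do not use severity.
- A reader might fault the plan for omitting lineage and sampling date as confounders. The covariate lists are left open, so this is detail that a fuller document may supply.
- Sample splitting costs power in a cohort of unknown size and need not be compulsory.

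What does not stand is the suggestion that the whole matter can be left to an analysis plan. The protocol itself assigns the regression the role of support, and the sequence it describes cannot provide it.

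**Conclusion.** The concern holds in a limited form. As described, the regression apparently reuses the patients and the outcome that selected the mutations, so its p-values and intervals are not independent support. Given that a chance association has been selected, the same-patient regression supports it in 27% to 93% of cases when five sites are forced in, and in 73% to 100% under threshold rules. In separate patients the rate is near the nominal 5%, with the strict-rule estimates imprecise.

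These figures rest on an assumed 384 patients, assumed severe shares and site counts, and independent sites; linkage between mutations would change the counts. The overall false-positive rate of the pipeline cannot be determined from the documents and may be low under a strict Bayesian rule. The consequence is confined to the exploratory severity claim in Expected outcomes; sensitivity, specificity and predictive values of the assays are untouched.

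**What to change.** In the sequencing section:

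1. State that the logistic estimates for selected mutations are descriptive: adjusted effect sizes, without confirmatory p-values.
2. Report a permutation-based false-discovery rate. Permute the severity labels, preferably within lineage or calendar period, and rerun the whole selection-plus-regression pipeline each time.
3. Use the word support only where the regression is fitted in patients not used for selection, either a held-out part or an external cohort, if cohort size allows.

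The cost of the first two is a change of wording, computing time and a weaker claim; neither gives up discovery power. The third reduces power for discovery if part of the cohort is held out, which is why it is conditional.

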#### Nanopore point-of-care sequencing

The cDNA libraries will be quantified using Qubit fluorometer (ThermoFisher Scientific, Waltham, MA) and the sizes of the libraries will be measured using Agilent Bioanalyzer (Agilent Technologies, Santa Clara, CA). For nanopore sequencing in both Cameroon, amplified cDNA libraries from Nextera procedures will be end-repaired and ligated with adapter and motor proteins using 1D library prep kit according to the 1D library preparation protocol for amplicons. Nanopore libraries will be run on Oxford Nanopore flow cells (R9.4 or R9.5) either on a MinION MK1B or a GridION X5 (Oxford Nanopore Technologies, Oxford, UKo). We aim for a target read coverage level of 500–1000 reads per site and majority consensus genome sequences will be generated from the NGS data for target pathogens (e.g., EBOV) for analysis with BEAST. Sequence generated by nanopore will be evaluated for reliability using the Next Generation sequencing (Illumina) as gold standard.

### Ethical considerations

The present study will be conducted according to the declarations of Helsinki on ethical principles for medical research involving human subjects. (http://www.wma.net/en/30publications/10policies/b3/) Ethical clearance has been obtained from the Cameroon National Ethics Committee for Research on Human Health in Cameroon (http://www.cameroon-ethics.cm/fr/quisommesnous), under the reference N°2022/01/1430/CE/CNERSH/SP of January 20, 2022. Participants will provide their signed written informed-consent (see S1 and S2 Files), for illerate participants a fingerprinting system will be used alongsdide a translator whenever necessary; phlebotomy will be done by well trained personnel (venipuncture, oro/nasopharyngeal swabs) and performed by trained-staffs Privacy and confidentiality will be ensured, through the use of unique identifiers and a protected database. Laboratory results will be free of charge for clinical management whenever necessary. A data safety and monitoring will ensure for an appropriate monitoring of the study implementation, under the scientific advisory board of the CIRCB.

#### Statistical analysis

Data will be collected on standard tools (S3 File) by trained field epidemiologists and stored in a password-protected database to ensure confidentiality of participant data and their privacy at the local institution in Yaoundé-Cameroon, by experienced statisticians who will coordinate data management and analyses using SPSS software, according to Good Clinical Data Management Processes (GCDMP).

Diagnostic Performance will be evaluated regarding the sensitivity, specificity, positive/negative predictive values (with 95% Confidence Intervals) will be described using ddPCR as molecular gold standard assay (lower detection limit of 10 copies/test) and ELISA as serology gold standard, stratified by range of viral loads, Ct values, duration after symptom onset, target biomarkers and viral diversity. To provide the highest level of evidence, adjustments of confounders (age, gender, HIV status, onset of symptoms, site, etc) will be performed using logistic and linear regression, wherever applicable.

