
A major drawback of rRT-PCR for the detection of SARS-CoV-2 remains its suboptimal sensitivity and the absence of an absolute quantitative evaluation of SARS-CoV-2 viral load [12, 16]. By using digital droplet PCR (ddPCR) as gold standard (lower detection limit of 10 copies) to evaluate the performance of a rRT-PCR set at 38 cycle threshold (Ct) for positivity, the sensitivity reported by Yu *et al*. was substandard (~68%) [12] and similar to sensitivity reported by Zhao *et al*. (~67%) [16]. Interestingly, the Ct of qRT-PCR appears to be highly correlated with the copy number of ddPCR for both the ORF1ab (R2 = 0.83) and the nucleocapsid (R2 = 0.87) genes, while only 61.2% of single-gene positive samples on qRT-PCR were also detected on ddPCR (viremia ranging from 11.1–123.2 copies) [12]. In the frame, we also applied an in-house ddPCR assay targeting RdRp for SARS-CoV-2 detection on negative swabs after RTPCR. This developed assay accurately identified and quantified SARS-CoV-2 even at 2.9 copies per reaction (i.e. 28 viral copies/mL), thus suggesting an excellent analytical sensitivity. Moreover, as quantification per mL is highly dependent on the quality of sampling and extraction procedure, this assay includes an internal reference gene (RNAseP) for quality control. The presence of this reference gene excludes any eventual PCR inhibition and confirms successful RNA extraction, thus reducing substantially the risk of false negative results. Moreover, ddPCR will allow a linear quantitation of SARS-CoV-2 viral load, and the determination of viral load in clinical samples will henceforth supports an indepth interpretation of laboratory assays, which in turn will strengthen the strategy for case isolation, tracking and contact tracing. It is becoming common to assume that the Ct values from RT-PCR diagnostic tests are direct estimates of viral load and Ct values could serve in identifying non-infectious patients in spite of positive PCR or infectious samples in correlation to cell cultures. Even though using the Ct values as estimates of SARS-CoV-2 viral loads appears simple and routinely acceptable, it could be misleading and the risk of introducing errors might be consistent. Thus, using ddPCR at a second diagnosis level could help in an accurate quantitation of SARS-CoV-2 viral load and an appropriate management of SARS-CoV-2 positivity [12].

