### Specific objectives

**To integrate and improve the available infrastructure, methodologies, and expertise on COVID-19**. For this purpose, we will create a platform enabling researchers and clinicians to better integrate and coordinate their research and translate the project outcomes into scientific and clinical expertise for the management of COVID-19 infection within the African context;**To enhance the capacities of the involved centers in Cameroon to screen and detect individuals at risk for COVID- 19 infection, by putting in place effective screening mechanisms and facilities at core sites (based on molecular and serological detection methods and SARS-CoV-2 genome sequencing)**. In this frame, individuals will be considered at risk of COVID-19 infection according to surveillance case definition for human infection with novel coronavirus published by WHO [WHO/COVID-19/Surveillance/v2020.2, January 15 2020];**To determine the performance of sensitive and specific point-of-care molecular detection assay for SARS-CoV-2**. Previous data on Zaire Ebola virus suggested that the POC molecular test has comparable diagnostic accuracy to the conventional real-time, minimized the time to obtain a result, thereby allowing clinicians or public health staff to make expeditious decisions. In the COVID-19 case, nasopharyngeal and oropharyngeal swab, and saliva will be valid samples to obtain a rapid and non-invasive screening for all travelers arriving in Cameroon. Concordance with other molecular tests already available for COVID-19 will be assessed (Corman et al. 2020; Chu et al. 2020);**To apply a rapid and sensitive ddPCR-assay SARS-CoV-2 quantification method as complementary to the standard RTPCR for COVID-19 diagnosis**. This test (single-step ddPCR assay) will have the ability to detect SARS-CoV-2 genome at very low copies number, representing a chance to detect infected subjects before any symptom onset, and to reveal the presence of COVID-19 in the environment in close contact with infected individuals. Based on ddPCR, a linear evaluation of SARS-CoV-2 load will be also available;**To validate a large panel of serological assays to identify COVID-19-exposed or vaccinated persons and to follow-up of COVID- 19 convalescents or immunisation**. This panel will enable an appraisal of Nucleocapside (N) and Spike protein (S) used in screening for natural and artificial immunity respectively;**To evaluate the variability of circulating SARS-CoV-2 variants in Cameroon based on whole genome sequencing and phylogenetic approaches**. Through sequencing of SARS-CoV-2, evidence on the dynamics of COVID-19 from the lineage of origin to newly emerging variants will be delineated, with the goal in predicting the trends of SARS-CoV-2.

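### ddPCR is the only molecular reference for detection accuracy, so every RT-PCR or Xpert disagreement with it is scored as their error and ddPCR's own extra detections cannot be verified

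*Protocol article*

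**What the plan says.** The choice of reference is stated consistently. The Statistical analysis section sets diagnostic performance "using ddPCR as molecular gold standard assay (lower detection limit of 10 copies/test) and ELISA as serology gold standard". Under Molecular testing of COVID-19, the RT-PCR paragraph says "Results will be evaluated with reference to ddPCR" and the GeneXpert paragraph says "Accuracy will be evaluated using ddPCR as gold standard". Expected outcomes, under specific objective 1, again compares both with ddPCR.

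ddPCR is also something the study brings in. The fourth specific objective reads "To apply a rapid and sensitive ddPCR-assay SARS-CoV-2 quantification method as complementary to the standard RTPCR for COVID-19 diagnosis", and says that the assay "will have the ability to detect SARS-CoV-2 genome at very low copies number, representing a chance to detect infected subjects before any symptom onset". The Methods part of the Abstract lists ddPCR with RT-PCR, GeneXpert and antigen tests before saying that sensitivity and specificity will be evaluated.

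The background section on molecular diagnostics reports, from a cited study, a correlation between Ct and ddPCR copy number, "while only 61.2% of single-gene positive samples on qRT-PCR were also detected on ddPCR".

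For the point-of-care assay, the third specific objective adds: "Concordance with other molecular tests already available for COVID-19 will be assessed". Expected outcomes lists overall agreement for RT-PCR platforms and point-of-care devices without naming the comparator.

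**The concern.** A reference standard is taken to be right by definition. That is acceptable when its accuracy is established elsewhere, or when the question is only how closely other assays follow it. Here one stated aim is that ddPCR finds infections that standard RT-PCR does not. If ddPCR also defines infection, that aim is assumed: a ddPCR-only positive is a missed case whether it is a real low-copy infection or a ddPCR false positive. In the other direction, a sample that RT-PCR or Xpert detects and ddPCR does not is an error of RT-PCR or Xpert, even where ddPCR missed the virus.

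The study intends to inform policy-makers on confirmation assays and to derive threshold values for interpreting RT-PCR. Accuracy figures, and any thresholds judged against ddPCR, would carry its errors without a signal that they do. The article names no composite reference, discordant resolution or follow-up by which ddPCR-only positives could be judged.

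**Working it through.** **1. Inputs**

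- Planned N = 1,536 (Sample size). The formula there reproduces: 1.96² × 0.51 × 0.49 / 0.05² = 384.0, and 1,536 = 4 × 384. N sets only the counts below; it cancels out of the percentages.
- Positivity: 51% (Sample size; assay not stated, taken here as RT-PCR positivity) and 20.39% (Description of the Cameroonian settings, by RT-PCR: 1,016 / 4,982 = 20.39%).
- RT-PCR sensitivity against ddPCR: about 68% (background, one cited study; another gives about 67%).
- Single-gene RT-PCR positives not detected on ddPCR: 100 − 61.2 = 38.8% (background).
- True ddPCR accuracy against infection: not in the documents, so assumed over a range.

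**2. What the scoring rule does**

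| Result pattern | Scored as |
|---|---|
| ddPCR positive, RT-PCR or Xpert negative | false negative of RT-PCR or Xpert |
| ddPCR negative, RT-PCR or Xpert positive | false positive of RT-PCR or Xpert |

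No cell can count against ddPCR. The 38.8% shows that disagreement in the second direction occurs in practice. It applies to single-gene positives only. The RT-PCR interpretation rule in this article is hard to read and may call some of those samples negative, so 38.8% is not a rate for all RT-PCR positives.

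**3. If ddPCR has imperfect specificity only**

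Assume that ddPCR misses no infection and that every RT-PCR positive is infected and ddPCR-positive. This simplifies, since step 2 shows that the overlap is not complete.

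RT-PCR positives R = N × positivity. ddPCR positives D = R / 0.68. With ddPCR specificity sp, D = I + (1 − sp)(N − I), so infected I = [D − (1 − sp)N] / sp. True RT-PCR sensitivity = R / I.

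| Positivity | R | D | ddPCR-only (D − R) | sp | I | R / I |
|---|---|---|---|---|---|---|
| 51% | 783.4 | 1,152.0 | 369 | 0.97 | (1,152.0 − 46.1)/0.97 = 1,140.1 | 68.7% |
| 51% | 783.4 | 1,152.0 | 369 | 0.95 | (1,152.0 − 76.8)/0.95 = 1,131.8 | 69.2% |
| 20.39% | 313.2 | 460.6 | 147 | 0.97 | (460.6 − 46.1)/0.97 = 427.3 | 73.3% |
| 20.39% | 313.2 | 460.6 | 147 | 0.95 | (460.6 − 76.8)/0.95 = 404.0 | 77.5% |

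At 51% the effect is about 1 point, because few participants are uninfected. At 20.39% it is 5 to 10 points.

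**4. If ddPCR has imperfect sensitivity as well**

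Assume prevalence 51%, RT-PCR truly 68% sensitive and 99% specific, and errors of the two assays independent given infection status.

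| True ddPCR sensitivity / specificity | Apparent RT-PCR sensitivity | Apparent RT-PCR specificity | ddPCR+/RT-PCR− | of these truly infected |
|---|---|---|---|---|
| 100% / 100% | 68.0% | 99.0% | 251 | 251 |
| 95% / 99% | 67.3% | 95.7% | 246 | 238 |
| 90% / 97% | 65.9% | 92.5% | 248 | 226 |
| 85% / 95% | 64.4% | 89.5% | 250 | 213 |

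The discordant count stays near 250 while the true detections in it fall from 251 to 213. The count alone cannot show what ddPCR adds. At 20.39% prevalence the counts are 100, 107, 127 and 146, with 100, 95, 90 and 85 truly infected.

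Independence matters. If both assays miss the same poor or low-copy swabs, the apparent RT-PCR sensitivity can be too high instead of too low, so the direction of the bias is not fixed either.

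**The case against.** The strongest reply is that the article does not promise an accuracy estimate for ddPCR. The fourth objective says apply, as a complement and for quantification. The accuracy outcomes in Expected outcomes cover RT-PCR platforms, point-of-care devices, and antigen and antibody tests. The Ct-to-load correlation needs no accuracy score for ddPCR. All of this stands. A reader might infer that the study will report ddPCR as 100% accurate or name it the best strategy; the documents do not say so. The sentence on "definition of the diagnostic strategy with the highest level of accuracy for a molecular and a rapid test" stands beside rapid-test algorithms and does not rank ddPCR against RT-PCR.

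A reader might also infer that Xpert is never compared with RT-PCR. The third objective promises that concordance, so the comparison is planned. The remark there about accuracy comparable to conventional real-time PCR is background from Ebola, not an equivalence aim of this study. Nor would an Xpert that performs like RT-PCR necessarily look like a failure: both are scored against ddPCR, so about 68% would stand beside about 68%. What remains is that the analysis section does not carry the promised concordance through. On its own that is minor, and a fuller plan may hold the detail.

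The reply that the whole matter can wait for a fuller plan does not succeed. The article states the reference and the scoring that follows from it. Complementary use for diagnosis, and detection before symptoms, are diagnostic claims that this scoring cannot check.

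**Conclusion.** The point holds in a limited form. With ddPCR as the sole molecular reference, the planned results measure agreement with ddPCR. They cannot show whether its extra positives are true detections, and they pass any ddPCR error to the RT-PCR and Xpert figures and to any RT-PCR threshold judged against it.

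The documents do not give the size. Under step 3, ddPCR specificity of 95% to 97% shifts RT-PCR sensitivity by about 1 point at 51% positivity and by 5 to 10 points at 20.39%. Those figures assume perfect ddPCR sensitivity and full overlap of RT-PCR positives with ddPCR positives. A claim of large bias at the article's design positivity of 51% is not supported by this calculation. The change is worth making because it costs little and limits what can be concluded.

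**What to change.** In the Statistical analysis section:

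- **Relabel.** Report the ddPCR-referenced results as positive and negative agreement with ddPCR, with paired discordant counts in both directions for RT-PCR and for Xpert. State that they will not be used to conclude that ddPCR is more accurate than either.
- **Carry the third objective through.** Name positive and negative agreement of Xpert with conventional RT-PCR, with 95% confidence intervals, as the planned concordance analysis.
- **Add two alternative references, beside the ddPCR result and not in place of it.** (i) Positive if ddPCR is positive, or if RT-PCR and Xpert are both positive. (ii) Positive if at least two of the three are positive, or if a SARS-CoV-2 sequence is obtained. Show RT-PCR and Xpert accuracy under each.

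The cost is wording and a few tables from data already planned; no new participants, samples or assays. There is a real downside. Both composites contain the tests being judged. The second calls a true very-low-copy, ddPCR-only infection negative unless it is sequenced, and sequencing is planned only in a subset (n = 384). A positive on RT-PCR alone or Xpert alone also stays negative under both, unless sequenced under the second. The composites are sensitivity analyses that bracket the result, not strict limits, and they must not be used to rank ddPCR.
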